#### Muscle strength

To investigate the effect of the prehabilitation program on muscle strength, a trained physical therapist will measure handgrip strength and quadriceps strength at baseline for both groups and after three weeks of prehabilitation for the prehabilitation group.

Handgrip strength (recorded in kilograms) will be assessed using the Jamar dynamometer (Sammons Preston, Rolyon, Bolingbrook, IL, USA) [48]. Handgrip strength has shown to be an indicator of skeletal muscle mass and a predictor of the risk of postoperative complications [49, 50]. The test will be performed in upright position with the elbows stretched in a straight line downwards, starting with the dominant hand. First, the handle position, in which the patient has maximum strength, will be determined. Patients will be asked to squeeze the handle as forcefully as possible for about two seconds. Hereafter, two more measurements will be performed (three grip measurements per hand). Each measurement will be followed by a pause of 15-20 seconds. Mathiowetz [48] compared the Jamar and Rolyan hydraulic dynamometers for measuring grip strength, and showed that the Jamar and Rolyan dynamometers have acceptable concurrent validity with known weights, excellent inter-instrument reliability, and strong concurrent validity.

Quadriceps strength (recorded in Newton) will be measured with a hand-held dynamometer (MicroFET2, Hoggan Health Industries Inc., West Jordan, UT, USA), which has been shown to be a feasible, inexpensive, and portable test of the quadriceps muscle strength for use in healthy older people [51]. Patients will be seated at the examination table with their lower limbs bent over the edge (knees and hips flexed at 90°). If necessary, additional stabilization will be provided at the patients’ shoulders by a second examiner. The test will be performed three times per leg, starting with the dominant leg. The hand-held dynamometer will be placed on the anterior aspect of the tibia at the level of the malleoli. The physical therapist will give resistance in the opposite direction. The patient must hold the leg in place. The resistance will gradually be increased in six seconds till maximum resistance/strength. The measurement will be stopped when the patient moves his leg. Each measurement will be followed by a pause of 30 seconds.

#### Functional mobility

To test (changes in) functional mobility, the physical therapist will execute the timed up-and-go (TUG) test at baseline for both groups and after three weeks of training for the prehabilitation group. The TUG test, a reliable and valid test, measures the time (recorded in seconds) a patient needs to stand up from a standard arm chair (approximate seat height of 46 cm), walk three meters, turn, walk back to the chair, and sit down again [52, 53]. The patient will perform the test once before being timed, in order to become familiar with the test and therefore minimize the learning effect.

In the literature, there are a few studies that demonstrated the use of the TUG test to identify patients at risk for impaired postoperative outcome [52, 54, 55]. Huisman et al. [55] showed that the TUG test was an independent predictor of the occurrence of major complications in a onco-geriatric surgical population. In this study, the predictive value of the TUG test on postoperative outcome will be determined. The TUG test is easy to perform, cheap, and does not need special equipment and might therefore be an alternative for the CPET.

#### Nutritional status

Assessment of nutritional status using the short nutritional assessment questionnaire (SNAQ) score [56] is part of usual care for our patients undergoing colorectal resection, and is evaluated at baseline for both the intervention and control group. The SNAQ is an easy, short, valid, and reproducible questionnaire for early detection of malnutrition [56]. Patients with a SNAQ score of 2 require nutritional support, whereas patients with a SNAQ score ≥ 3 require supervision by a dietician and nutritional support. In this study the SNAQ score will be used as a baseline characteristic.

#### American Society of Anesthesiologists score

The American Society of Anesthesiologists (ASA) score is the most widely used system to describe a patient’s preoperative health status. The ASA score has five classes ranging from class I, a completely healthy patient, to class V, a moribund patient who is not expected to live 24 hours with or without surgery [57, 58]. The ASA score will be assessed at baseline for both groups.

#### World Health Organization performance scale

The World Health Organization (WHO) performance scale is a tool to assess how a patient’s disease is progressing, how it affects activities of daily life, and it helps the clinician to determine appropriate treatment and prognosis [57]. The WHO performance scale will be assessed at baseline in the prehabilitation group and in the usual care group.

#### Charlson comorbidity index

The Charlson comorbidity index [59, 60] will be scored at baseline for the prehabilitation group and usual care group. It can be a useful preoperative tool in predicting morbidity and mortality outcomes in patients with colorectal cancer [61].

#### Questionnaires

Every patient will visit an oncology nurse prior to colorectal resection, which is part of usual care. The oncology nurse will ask the patient to fill out several questionnaires: the instrumental activities of daily living (IADL) [62–64], geriatric depression scale 15 (GDS 15) [65, 66], the quality of life questionnaire of the European organization for research and treatment of cancer (EORTC QLQ-C30) [67, 68], and the Groningen frailty indicator (GFI) [69]. The IADL will investigate whether a patient experiences difficulties in carrying out instrumental activities that are essential to independent living. The GDS 15 will be used to measure perceived depressive symptoms or emotional health, and has good reliability, validity, sensitivity, and specificity for older people [70]. Patients will answer ‘yes’ or ‘no’ to fifteen questions depending on how they have felt over the past week. A score of 0-4 indicates normal mood or emotional health status, 5-9 indicates mild depression, and 10-15 indicates moderate-to-severe depression. The EORTC QLQ-C30 is a reliable and valid measure of the perceived health-related quality of life of patients diagnosed with cancer in multicultural clinical research settings [67]. The GFI is a short and easy-to-use instrument to measure frailty, which is defined as a loss of resources in several domains of functioning, which leads to a declining reserve capacity for dealing with stressors [69]. The patient will be asked to fill out the IADL, GDS 15, and GFI for the second time 30 days after surgery in order to investigate the effect of surgery on the IADL, depression, quality of life, and frailty, in both the prehabilitation and usual care group.

A limited geriatric assessment will be performed at baseline for the prehabilitation group and the usual care group, measuring comorbidity with the Charlson comorbidity index, signs of depression using the GDS 15, and functional status using the IADL. We will investigate the value of the limited geriatric assessment to predict postoperative complications. In addition, the GFI will be used in order to examine whether a screening tool can replace this limited geriatric assessment.

Illness perception will be recorded in both groups by using the brief illness perception questionnaire, a quick and easy to use questionnaire [71]. The face and content properties were found to be acceptable, and the reproducibility showed moderate-to-good reliability [71]. Illness perception is an important factor of health. Patients’ personal thoughts about the symptoms they experience can be seen as one of the psychosocial factors by which variance in physical functioning in patients can be explained [71]. The physical therapist will ask patients in the prehabilitation group to fill out the brief illness perception questionnaire again after the three-week training period, in order to investigate the effect of the prehabilitation program on illness perception.

Health status will be evaluated by using the EuroQol 5D (EQ-5D) [72]. The EQ-5D questionnaire is a short profile measure of perceived health-related quality of life, and has five domains: 1) perceived mobility, 2) self-care, 3) usual activities, 4) pain/discomfort, and 5) anxiety/depression. Each domain is scored by patients according to three levels (no problems, some problems, extreme problems), for which quality weights (to enable calculation of quality adjusted life years for use in economic evaluations) are available [73]. The EQ-5D is widely used in oncology and it has shown a reasonable degree of reliability, content validity, construct validity, and responsiveness in the majority of available studies [74]. The physical therapist will ask patients in the prehabilitation group to fill out the EQ-5D again after the three-week training period, in order to investigate the effect of the prehabilitation program on health status.

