### Measurements

Both the prehabilitation group and usual care group will participate in a series of outcome measure assessments at baseline, seven days postoperatively, and 30 days postoperatively, whereas the prehabilitation group will participate in a series of outcome measure assessments after the three-week prehabilitation program as well (see Table 3).

**Table 3 Tab3:** Schedule of enrolment, interventions, and assessments

STUDY PERIOD	Enrolment	Allocation	Post-allocation					Follow-up	
			Pre-prehabilitation	Prehabilitation			Post-prehabilitation		
TIMEPOINT	-t_1_	0		Week 1	Week 2	Week 3		Day 7 post-surgery	Day 30 post-surgery
ENROLMENT:									
Eligibility screening	X								
VSAQ score (METs)	X								
Informed consent	X								
Allocation		X							
CPET	X								
INTERVENTIONS:									
Intervention group (prehabilitation program)									
Usual care group									
ASSESSMENTS:									
Baseline characteristics	X								
SNAQ score (0-5)	X								
VAT on CPET (mL/kg/min)			X				X^a^		
TUG test (s)			X				X^a^		
Muscle strength test			X				X^a^		
IADL			X						X
GDS 15			X						X
EORTC QLQ-C30			X						
GFI			X						X
Brief illness perception questionnaire			X				X^a^		
EQ-5D			X				X^a^		
Postoperative complications								X	X

^a^: Only for patients in the prehabilitation group

Abbreviations: CPET, cardiopulmonary exercise test; EORTC QLQ-C30, quality of life questionnaire of the European organisation for research and treatment of cancer; EQ-5D, EuroQol 5D; GDS 15, geriatric depression scale 15; GFI, Groningen frailty indicator; IADL, instrumental activities of daily living; MET, metabolic equivalent of task; SNAQ, short nutritional assessment questionnaire; TUG, timed up-and-go; VAT, ventilatory anaerobic threshold; VSAQ, veterans-specific activity questionnaire

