#### Statistical analysis

Nominal variables will be presented as numbers with percentages. Continuous variables will be presented as mean ± SD, or as median and interquartile range, as appropriate. Data will be presented in tables and figures. All tests will be performed on the intention to treat population, and on the per-protocol population. Data distribution will be checked with help of an epidemiologist.

For categorical variables, chi-squared tests or Fisher’s Exact tests, as appropriate, will be performed to analyze the difference between the intervention and control group. For continuous variables this will be done by independent samples t-tests or Mann-Whitney U tests, as appropriate. A repeated measurements analysis (mixed models in SPSS) will be performed to assess changes over time in continuous variables. A cost-effectiveness analysis will be performed, with the use of quality adjusted life years. Withdrawn patients will be followed by checking the patient’s data file. We will use the intention-to-treat analysis to avoid various misleading artifacts.

When half of the patients needed that are calculated (43 patients) are included, a blinded independent data analyst will perform an interim analysis with a stopping rule according to O’Brien-Fleming [81]. If this interim analysis shows a significant difference in postoperative complications between the prehabilitation group and the usual care group (at *P* < 0.0054), this data analyst will contact the Medical Ethics Committee, and debate the outcome of the interim analysis and its eventual repercussions. Thereupon this committee will advise the principle investigator of the research team (JK) to decide to stop the inclusion in case of superiority. If the interim analysis shows no or minimal difference (< 10% on overall complications), the study will be stopped due to futility. Because of the interim analysis, the final *P*-value that is considered to be significant is reduced to *P* < 0.0492.

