The present study, like all studies do, bares some limitations. Firstly, merely patients in the prehabilitation group will perform a second CPET to investigate the effect of the prehabilitation program on cardiorespiratory fitness. Consequently, we are not able to investigate the changes in cardiorespiratory fitness in the preoperative waiting period in the usual care group. However, the waiting period in patients in the usual care group was kept as short as possible to prevent these patients to improve their level of fitness by organizing their own preoperative exercise training program. Moreover, a study in patients planned for elective hepatic resection for colorectal liver metastases reported no significant differences in CPET variables in the control group after a four-week waiting period [25]. Secondly, the prehabilitation program in the present study consists only of a preoperative exercise training program, while it was recently indicated that studies evaluating a prehabilitation program combined with a nutritional intervention before elective major surgery in adults are producing encouraging early results [31]. However, definitive clinical evidence of physical and nutritional prehabilitation is currently very limited [31, 85, 86]. Thirdly, up till now, patient inclusion appears to be challenging. Not all patients are able and/or willing to attend the prehabilitation program due to personal, logistical, and time limitations (e.g., restricted time availability between the first outpatient visit and surgery, living too far away from the community physical therapy practice, and/or no traveling opportunities, planned vacation prior to surgery, not interested in participation). Moreover, at the start of the present study patients in both groups were informed about the possible effects of prehabilitation. We experienced that some patients in the usual care group initiated preoperative physical exercise training themselves, possibly resulting in the risk that we will not be able to detect a difference between the prehabilitation and usual care group. Therefore, we made an amendment to the study protocol (approved in April 2016 by the Medical Ethics Committee Twente) in which patients in the prehabilitation group and the usual care group will be informed differently. The patients in the usual care group will not receive information about the possible effects of prehabilitation and their elective colorectal resection was planned at the earliest convenience. Fourthly, in the present study a geriatric assessment will be completed at baseline only. Baseline data as predictors of postoperative outcome may be confounded by the effect of the prehabilitation program. Therefore, only data from patients in the usual care group will be used to investigate the value of a limited geriatric assessment to perform preoperative risk stratification. However, the power for this secondary objective might be inadequate, as the sample size calculation was not based on this objective.

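### Programme effects on muscle strength, illness perception and EQ-5D are claimed from repeat measurements taken in the prehabilitation group only

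*Protocol article*

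**What the plan says.** The Measurements section assesses both arms at baseline and on days 7 and 30 after surgery, "whereas the prehabilitation group will participate in a series of outcome measure assessments after the three-week prehabilitation program as well". In Table 3 the post-programme entries for VAT, timed up-and-go (TUG), muscle strength, brief illness perception and EQ-5D all carry footnote a: "Only for patients in the prehabilitation group". None of these five is scheduled again after surgery in either arm.

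The aims are worded as follows:
- Muscle strength: "To investigate the effect of the prehabilitation program on muscle strength", measured "at baseline for both groups and after three weeks of prehabilitation for the prehabilitation group".
- Illness perception (Questionnaires): repeated in the prehabilitation group "in order to investigate the effect of the prehabilitation program on illness perception". The EQ-5D paragraph gives the same aim for health status.
- TUG (Functional mobility): "To test (changes in) functional mobility". This speaks of change and claims no programme effect.

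For the CPET, the secondary objectives and the CPET section openly call the comparison single-arm. The first limitation in the Discussion concedes that change in usual care cannot be studied, but for cardiorespiratory fitness only.

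The Discussion also reports, of controls: "We experienced that some patients in the usual care group initiated preoperative physical exercise training themselves". The response was an amendment approved in April 2016. The arms are now informed differently, and surgery for usual care patients is planned as early as possible.

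**The concern.** A programme effect is the difference between what happened with the programme and what would have happened without it. Usual care has no assessment between baseline and surgery, so the second quantity is not observed for strength, illness perception or EQ-5D. Perceptions of illness and health may shift in the weeks between diagnosis and operation whatever the patient does, and repeated physical tests can improve with familiarity. The Functional mobility section itself provides a practice run to reduce learning on the TUG. If the aims are followed as worded, all such change would be reported as the work of the programme.

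EQ-5D deserves particular care. Statistical analysis plans a cost-effectiveness analysis using quality-adjusted life years, while Table 3 lists EQ-5D for usual care at baseline only.

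The same empty interval is where controls are reported to have trained themselves. Neither Table 3 nor the list under Other study parameters shows an item that would describe how often this happened.

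**Working it through.** **1. Aim against schedule.**

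| Measure | Aim as worded | Usual care, baseline to surgery | Single-arm label or stated limitation |
|---|---|---|---|
| VAT (CPET) | observe change | none | yes, both |
| Muscle strength | programme effect | none | no |
| Illness perception | programme effect | none | no |
| EQ-5D | programme effect | none | no |
| TUG | change | none | no |

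The three middle rows combine causal wording with one-arm data and no caveat. TUG shares the missing control but not the causal wording.

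**2. What a one-arm test estimates.** Mean observed change = programme effect + background change. With one arm only the sum is estimated. Suppose the programme does nothing and the background change is b standard deviations of the change score. A two-sided 0.05 paired test on n patients then declares an effect with probability

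Φ(−1.96 + b√n) + Φ(−1.96 − b√n).

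Take n = 39, the article's group size before dropout, so √39 = 6.245. The values of b are assumed, as the article gives none.
- b = 0.1: b√n = 0.62, probability 0.096
- b = 0.2: b√n = 1.25, probability 0.239
- b = 0.3: b√n = 1.87, probability 0.466

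**3. The article's own sample size.** Inputs from Sample size calculation: 50% against 20%, alpha 0.0492 (taken as two-sided), power 0.80.

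n = [1.967 × √(2 × 0.35 × 0.65) + 0.842 × √(0.25 + 0.16)]² / 0.30² = (1.327 + 0.539)² / 0.09 = 38.7, so 39 per group. Then 39 × 1.10 = 42.9, so 43. Both stated figures are reproduced, and no figure is in dispute.

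**4. Upper bound for self-training.** Assume a fraction c of controls trains and gains the whole planned benefit. The control rate becomes 50% − 30c percentage points. Power at 39 per arm, using the same normal approximation:
- c = 0: 50%, power 80.3%
- c = 0.1: 47%, power 72.0%
- c = 0.2: 44%, power 62.4%
- c = 0.3: 41%, power 51.9%

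The article does not give c, and full benefit from unsupervised training is a worst case.

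**The case against.** The one-arm schedule is deliberate and openly stated wherever these measures appear. The repeated-measures model in Statistical analysis suits one-arm repeats, and the article nowhere promises a between-arm test of change in strength, illness perception or TUG. None of the three is a primary or secondary parameter. All of this stands, and it limits the importance of the point. It does not remove the mismatch between an aim worded as an effect and data that can show only change.

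A reader might go further and infer that self-training is never recorded and that the per-protocol analysis will count self-trained controls as untreated. The documents do not support this. Statistical analysis says "All tests will be performed on the intention to treat population, and on the per-protocol population" without defining the per-protocol set. An article that condenses a longer protocol commonly leaves such definitions and form items to that protocol. It can be said only that no record is listed here.

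A reader might also take the 72% to 52% power range as the size of the problem. It is a worst case in an unknown fraction, and recording exercise would not win back any of that power. The article already discloses the risk and acted to reduce it.

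**Conclusion.** The point holds for muscle strength, illness perception and EQ-5D. Their stated purpose is a programme effect, their design is uncontrolled, and the caveat given for cardiorespiratory fitness is not extended to them. TUG needs the caveat but no rewording of its aim.

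The size cannot be fixed from the document. The false-effect rates of about 10%, 24% and 47% rest on assumed background changes of 0.1 to 0.3 SD and on all 39 participants completing the repeat. They show that modest drift would be enough to mislead.

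The missing repeats do not bias the randomised comparison of complications, which remains valid by intention to treat. Self-training is a secondary matter: it is reported and mitigated, and the article lists no means of describing its extent.

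**What to change.** **Minimum, no new data.** In Muscle strength and in both Questionnaires paragraphs (illness perception and EQ-5D), replace the wording on the programme's effect with *change during the programme in participants*. Extend the first limitation in the Discussion to strength, illness perception, EQ-5D and TUG.

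**Alternative, for patients still to be enrolled.** Give both arms the brief illness perception questionnaire and EQ-5D at a pre-surgery contact such as admission, as a Table 3 column without footnote a. Compare arms adjusted for baseline. Record the interval since baseline, because the timing of surgery, and of radiotherapy where given, can differ between arms. Strength and TUG would keep the reworded aim or caveat.

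**Self-training.** At that same contact, ask both arms one or two questions on exercise since baseline. Use the answers to describe contamination and at most in a sensitivity analysis. Keep intention to treat primary and do not exclude self-trained controls: selecting one arm on self-reported behaviour after randomisation would itself introduce bias. Any split of results at April 2016 should be descriptive only, as the groups are small and confounded with calendar time.

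**Cost.** A few minutes of forms per patient, plus wording. Questions asked at admission come too late to prompt training. Patients already operated on will have no such data.

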The primary objective of this randomized controlled trial is to evaluate the hypothesis that a three-week prehabilitation program (intervention group) will reduce the number of postoperative complications from 50% to 20% in patients with a preoperative VAT < 11 mL/kg/min who will undergo elective colorectal resection for colorectal cancer or dysplasia grade I, II, or III, when compared to usual care (control group).

The secondary objectives are 1) to observe whether changes in preoperative cardiorespiratory fitness occur in the intervention group (prehabilitation, single-arm study design), 2) to evaluate the effect of the prehabilitation program on length of stay, 3) to examine whether patients with a preoperative VAT ≥ 11 mL/kg/min, and who will therefore not be included in the randomized controlled trial, have fewer postoperative complications than patients in the prehabilitation or usual care group (for the prehabilitation group, we will use the post-prehabilitation CPET data), 4) to investigate the value of a limited geriatric assessment in this patient group to perform preoperative risk stratification, and 5) to evaluate the cost-effectiveness of prehabilitation in high-risk patients by performing a cost-effectiveness analysis.

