
We believe that preoperative exercise training in patients ‘merely’ undergoing elective colorectal resection will be only cost-effective and sustainably implementable in usual care pathways when performed in high-risk patients (those with a low cardiorespiratory fitness, e.g., a VAT < 11 mL/kg/min). Hence, an adequate preoperative risk stratification protocol, such as the protocol used in the current study (a CPET for patients with a VSAQ score < 7 METs, of which those patients with a VAT < 11 mL/kg/min at the CPET will be eligible for and advised to participate in prehabilitation), will probably lead to a feasible sustainable implementation of the prehabilitation concept. For patients undergoing elective colorectal resection and (neo)adjuvant chemotherapy and/or radiotherapy, prehabilitation might be cost-effective in all patients. Cost-effectiveness should be expected, and therefore evaluated, in terms of, among other things, fewer postoperative complications, fewer reoperations, less intense clinical care, a shorter length of stay, a more effective surgical planning (process-optimization), fewer readmissions, less intense rehabilitation, shorter rehabilitation period, and earlier resumption of work.

The strengths of our present study are the selection of high-risk patients, the clear description of the study design and prehabilitation program, the 1:1 randomization between the prehabilitation and usual care group, the use of validated measurement instruments, and the adjustment of the physical exercise training program to the cardiorespiratory fitness of the individual patient based upon the results of the CPET. Moreover, prehabilitation will be performed in a community physical therapy practice in the catchment of the patient’s home. In this way we will try to reach the frailest patients who are not capable to visit the hospital each time.

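### The QALY part of the cost-effectiveness analysis cannot be estimated as a randomised comparison from the EQ-5D data that the trial schedules

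*Protocol article*

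**What the plan says.** Secondary objective 5 in the Background is "to evaluate the cost-effectiveness of prehabilitation in high-risk patients by performing a cost-effectiveness analysis". The Statistical analysis section gives the metric: "A cost-effectiveness analysis will be performed, with the use of quality adjusted life years". The Questionnaires section links this to the EQ-5D, for which "quality weights (to enable calculation of quality adjusted life years for use in economic evaluations) are available". No other instrument is given that role.

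On timing, the Measurements section says that both groups "will participate in a series of outcome measure assessments at baseline, seven days postoperatively, and 30 days postoperatively". That sentence names no instrument and points to Table 3. In Table 3 the EQ-5D row is marked before prehabilitation and again after prehabilitation. The second mark carries a footnote: "Only for patients in the prehabilitation group". The cells for day 7 and day 30 after surgery are empty. The Questionnaires text says the same: "The physical therapist will ask patients in the prehabilitation group to fill out the EQ-5D again after the three-week training period".

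For the day-30 contact the text says: "The patient will be asked to fill out the IADL, GDS 15, and GFI for the second time 30 days after surgery". The stated purpose of that repeat includes the effect of surgery on quality of life. The EORTC QLQ-C30 is not among the three instruments listed, and Table 3 marks it at baseline only.

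**The concern.** A QALY difference between randomised arms needs utilities over time in both arms, across the period in which the treatment is expected to act. The Discussion expects savings through "fewer postoperative complications, fewer reoperations, less intense clinical care, a shorter length of stay", all of which arise after surgery. The schedule gives no follow-up utility in usual care and no postoperative utility in either arm. Followed as written, the trial reaches its analysis with a stated metric and no data to form it. An analysis plan can choose a method but cannot supply measurements that were never taken, and every patient who passes day 30 is lost for this purpose.

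A smaller mismatch sits beside it. The effect of surgery on quality of life is a declared purpose of the day-30 questionnaires, yet the trial's cancer quality-of-life instrument is not repeated then.

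**Working it through.** The plan gives no figure for the QALY analysis, so there is none to reproduce. The check reads the schedule cell by cell and then sizes what is missing.

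**1. Schedule (Table 3, confirmed by the Questionnaires text)**

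| Time | Prehabilitation | Usual care |
|---|---|---|
| Baseline | EQ-5D, QLQ-C30 | EQ-5D, QLQ-C30 |
| After training, before surgery | EQ-5D | none |
| Day 7 after surgery | no EQ-5D | no EQ-5D |
| Day 30 after surgery | IADL, GDS 15, GFI; no EQ-5D, no QLQ-C30 | IADL, GDS 15, GFI; no EQ-5D, no QLQ-C30 |

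A broken table does not explain the gap. The IADL, GDS 15 and GFI rows keep their day-30 marks, and the text names exactly those three.

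**2. What a QALY needs**

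For one patient with utilities u at times t (in years), QALY = Σ (u_j + u_{j+1})/2 × (t_{j+1} − t_j). This needs at least two utilities.
- Prehabilitation: 2 utilities, both before surgery. The area covers roughly the three training weeks.
- Usual care: 1 utility. No area can be formed.
- After surgery: 0 utilities in either arm, for all 2 × 43 = 86 planned patients.

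**3. Size of the unobserved part (assumption: a constant utility difference δ between arms over the 30 postoperative days)**

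δ × 30/365.25:
- δ = 0: 0
- δ = 0.05: 0.0041
- δ = 0.10: 0.0082
- δ = 0.20: 0.0164 QALY

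**4. What carrying the last value forward would give**

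The usual care change is zero by construction. Let c be the change in the prehabilitation arm over training, linear over 21 days and then held for 30 days. The contrast is c/2 × 21/365.25 + c × 30/365.25.
- c = −0.05: −0.0014 − 0.0041 = −0.0055
- c = 0.05: +0.0055
- c = 0.10: 0.0029 + 0.0082 = 0.0111 QALY

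The values of c are assumptions. Whatever c is, the contrast comes only from a preoperative change in one unblinded arm and contains nothing about complications.

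**5. Why the horizon matters for any repair**

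Day 30 is counted from surgery. The prehabilitation arm trains for three weeks first, while the Discussion says that surgery in usual care was scheduled as early as possible. If QALYs run from baseline to postoperative day 30, the arm that waits longer gains QALYs merely from the extra time. With an assumed utility of 0.8:
- 1 week longer: 0.8 × 7/365.25 = 0.015 QALY
- 3 weeks longer: 0.8 × 21/365.25 = 0.046 QALY

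That is about as large as, or larger than, the largest effect in step 3.

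**The case against.** The strongest reply is that the QALY promise is narrower than it looks. Objective 5 and the matching secondary parameter speak of cost-effectiveness without naming QALYs. The metric appears in one sentence of the Statistical analysis section, and the Discussion lists complications, reoperations, stay and readmissions among the terms in which cost-effectiveness should be judged. A reader might infer that the whole secondary objective is unanswerable. The document does not support that: cost per patient without a complication could still address it, provided costs are collected.

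A reader might also infer that no QALY figure can be produced at all. That goes too far as well. A decision model that applies published utilities to observed complications would yield a number, and an article may leave such a model to a fuller economic plan. But the article names no model and no outside utilities, and it presents the EQ-5D as the source of weights. A modelled figure would not be a comparison of utilities measured in the randomised arms.

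The repeat EQ-5D does serve its own stated purpose, an uncontrolled look at health status after training, in line with the openly single-arm second CPET. The absolute QALY amounts are also small, and the primary endpoint, sample size and interim analysis are untouched. These points limit the scope. They do not close the gap between the stated metric and the schedule.

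**Conclusion.** The point holds for the within-trial QALY component only. Text and table agree that the EQ-5D is measured once in usual care, twice before surgery in prehabilitation, and never after surgery. No randomised QALY contrast can be formed from those data without assuming the usual care path and both postoperative paths. The schedule reading rests on no assumption. The QALY amounts do: utility differences of 0 to 0.20, training changes of −0.05 to +0.10 and a utility of 0.8 are illustrative and do not come from the document. The missing day-30 QLQ-C30 is a separate and minor inconsistency, and adds no weight to the QALY point.

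**What to change.** - Amend Table 3 and the Questionnaires text so that both arms complete the EQ-5D at the existing day-30 questionnaire contact, and usual care also completes it before surgery where a contact exists.
- Add the QLQ-C30 to the day-30 set, or remove quality of life from the stated purpose of that repeat.
- Calculate QALYs over a horizon of equal length in both arms, counted from randomisation or baseline and not ending at postoperative day 30. State how utility is handled between a patient's last EQ-5D and the end of the horizon.
- For patients already past day 30, or if the schedule is not amended, withdraw the within-trial QALY claim. Report cost per patient without a complication, provided costs are collected, or prespecify a model with a named utility source.

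The cost is a short amendment and one or two brief questionnaires per patient. The trial started in February 2014 and inclusion was expected to end in 2018, so QALY data will stay incomplete for patients already enrolled, and the report should say so.
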